### Randomization and blinding

Following the baseline measurement, participants are randomized at a 1:1:1 ratio to one of three conditions. The randomization sequence was generated by the study statistician using a computer program in variable blocks (3 and 6), stratified by sex [58]. Allocation was concealed in consecutively numbered, opaque sealed envelopes. Given the nature of the intervention, participants are aware of the group to which they have been allocated. The outcome assessor will not be blinded to the treatment allocation, however, the assessment of cardiorespiratory fitness and physical activity levels utilize objective measures.

### Description of interventions

Participants randomized to the intervention groups receive either a non-immersive or immersive app (see description below), which is downloaded on their mobile device by AD. Once installed, participants receive a short instruction on the features and settings of the app and are encouraged to use it three times per week. No changes will be made to the intervention or study design once recruitment begins, however, participants can choose to stop receiving the intervention and will be informed of this during the consenting process.

The choice for the interventions was based on previous work conducted by the authors, which evaluated the top-40 most downloaded apps of the health and fitness category of the New Zealand iTunes store. In this study we rated "off-the-shelf" apps for the presence or absence of behavior change techniques [46]. The two apps selected included self-regulatory behavior change techniques previously shown to be effective in changing physical activity behavior (i.e. prompt intention formation, prompt specific goal setting, prompt self-monitoring, provide feedback on performance, and prompt review of behavior goals) [59], were focused on improving fitness, and were available in both the Apple and Android stores. Further, we were interested in comparing an app with an immersive story to an app without story since game-based stories that engage individuals can be used for health behavior change [24, 35] to model behaviors by immersing and capturing attention. Lastly, these apps are readily available to consumers and are inexpensive (NZ$2.45–4.19, depending on app store).

### Non-immersive app

Participants randomized to the non-immersive app group have the “Get Running—Couch to 5 K” (Fig. 3) app installed on their smartphone/iPod touch®. This app entails a 9-week training program delivered via headphones with three workouts a week (each during 35 min approximately) to help individuals run “even if getting off the couch is a struggle” [60]. The embedded human voice coach progressively enhances the user’s fitness until they are able to complete a 5 km distance.

### Immersive app

Participants randomized to the immersive app group have the “Zombies, Run! 5 K Training” app installed onto their device (Fig. 4). Likewise, the app consists of an 8-week training program; three workouts a week, each during 35 min approximately, that give detailed instructions via headphones about when to walk, jog, run and stretch. However, this app combines the training program with an immersing, fun story where the user needs to get fit to escape zombies. Despite its “fear themes” and “frequent/intense cartoon or fantasy violence” it is rated as suitable for an audience aged 12+ [61].

**Fig. 3 Fig3:**
[figure not shown]
Screenshot of the “Get running” app

**Fig. 4 Fig4:**
[figure not shown]
Screenshot of the “Zombies, run!” app

### Control (usual physical activity)

Participants randomized to the control group are asked to continue with their usual physical activities for the duration of the study. Both apps are offered to participants once they have completed the study.

Although the duration of the training program of the non-immersive app is 1-week longer than the immersive app, the programs are similar regarding their frequency and duration of sessions. All participants will be assessed 8-week post randomization.

### Outcomes

#### Primary outcome

The primary outcome is cardiorespiratory fitness, assessed with the one mile run/walk test, is a reliable and valid assessment of cardiorespiratory fitness [62, 63] that can be used to estimate oxygen consumption (VO_2_) in young people [64]. The test is used in the most important fitness test batteries for young people, such as Fitnessgram. Participants walk and/or run at their own pace until completing the distance in the shortest possible time. The total time (i.e. in minutes and seconds) to complete the course is recorded for each participant at both visits, which will be computed in seconds for subsequent analysis. Participants will complete the test individually, on an outdoor field-track on the University of Auckland campus sport grounds. Before the test, warm-up includes a walk on the track and a self-selected routine. The procedures listed in the test administration protocol will be followed [62], whereby participants will be instructed to “run the distance at the fastest pace possible” and asked to try to pace themselves in order to avoid running too fast early and then walk in the later stages. Even though the goal is to complete the distance as quickly as possible, it will be stressed that if one must walk, he/she should try a fast pace and not feel inferior. During the test, participants will be told times as they pass the start line—to assist with pacing—and encouraged with positive feedback. A list of typical encouragement sentences will be used to ensure consistency. Participants will report their rating of perceived exertion before and at the end of the assessment using the Children’s OMNI scale [65]. Following the test, participants will be free to walk around to cool-down and invited to stretch their leg muscles.

#### Secondary outcomes

The following secondary outcomes are assessed at baseline and 8 weeks.Anthropometrics (body mass index) are measured using standardized practices [66]. Bodyweight is measured to the nearest 0.1 kg using a calibrated scale (Salter), while height is measured to the nearest 0.1 cm using a stadiometer (Seca). Physical measurements are taken as the average of two readings.Self-reported physical activity is assessed using the Physical Activity Questionnaire for Adolescents (PAQ-A), a validated self-report seven day recall measure with good internal consistency (Cronbach alphas range from 0.72 to 0.85) and acceptable validity compared to an activity monitor (rho = 0.49) [67]. The PAQ-A items assess physical activity at school (i.e. physical education, lunchtime), after school, and at home (organized and recreational). Each statement is scored on a five-point scale with higher scores indicating higher activity levels. The final PAQ-A score is an average of eight items [68].Objectively measured physical activity is assessed using the GT1M Actigraph (http://www.actigraphcorp.com), a motion sensor shown to be a valid and reliable instrument for assessing physical activity in young people [69]. Participants are asked to wear the Actigraph following each assessment for seven consecutive days. They are instructed to wear the monitor during waking hours on their mid-axilla line right hip, removing it when engaging in activities involving water (e.g. water sports, showering) and contact sports. Participants are asked to complete a daily log detailing the time the Actigraph was put on and removed.The GT1M model was initialized to collect data in 10-s epochs [70]. The ActiLife software (version 5) [71] is used to initialize the accelerometers and download the data following wearing periods. All accelerometer data files are exported individually as a .csv file and aggregated into a combined .csv file that is imported into SAS. During subsequent processing, data are aggregated into minute intervals. To determine valid wear time, periods of more than 60 min of consecutive zeroes and days with less than 600 min of valid records are removed before data analysis [72]. All participants with at least 3 days of valid data will be included in the analysis [73]. The average daily time spent in sedentary, light, moderate, vigorous and moderate to vigorous activities is calculated for each participant. The Evenson cut points for defining activity intensities are used: sedentary <100, light >100, moderate ≥2296, vigorous ≥4012 [74–76].Perceived enjoyment of physical activity is assessed using the Physical Activity Enjoyment Scale (PACES) [77]. Participants rate their agreement with 16 statements on a five-point Likert type scale (e.g. “When I am active it gives me a strong feeling of success”). Factorial validity and gender invariance among older adolescents has been previously demonstrated [78]. Scores are summed with higher scores indicating higher level of enjoyment.The Psychological Need Satisfaction in Exercise Scale (PNSES) [79] is used to measure perceived competence, autonomy and relatedness while exercising. Participants rate their agreement with 18 items on a six-point Likert type scale (e.g. “I feel free to exercise in my own way”). Six items are referenced to each of the three domains. Construct validity and gender invariance for the PNSES have been previously documented [79].Self-efficacy is assessed using the Physical Activity Self-Efficacy Scale (PASES) [80]. This eight item questionnaire has well-established validity [81]. Items are scored from on a 3-point Likert-type scale (e.g. “I can be physically active most days after school”), with a higher summed score indicating higher self-efficacy.Self-reported frequency of app utilization (e.g. “How many times per week did you use the app?”), acceptability (e.g. Will you continue to use the app?”), and usability (e.g. “When did you use the app?”) of the apps are assessed via an exit survey conducted with all intervention participants. A series of open-ended questions are asked to determine the features participants considered most and least acceptable, as well as the ones they used most often to support their physical activity. Objective data on app usage (i.e. automatically logged in the background while features were accessed) was not possible to collect due to the apps not being developed by the research team and not being open source (i.e., could not be modified to suit investigation purposes).

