### Outcome assessments

Assessments are conducted at baseline and 8-week post randomization (see Fig. 2) at the University of Auckland clinics and sport grounds (duration 45 to 60 min, of which 10 to 15 min to complete self-reported measures). Baseline assessments involve an explanation of study procedures, signed consent and collection of participant-reported secondary outcomes, followed by physical measurements (height and weight) and a field test of cardiorespiratory fitness. Participants are then asked to wear an accelerometer for seven consecutive days. Randomization takes place at a subsequent visit to the participants’ home once baseline accelerometer data collection is completed.

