
### Statistical analyses

Treatment evaluation will be performed on the principle of intention to treat. Statistical analyses will be conducted using SAS version 9.3 software (SAS Institute, Cary, NC, USA). All statistical tests will be two-sided and maintained at a 5 % significance level. Apart from accelerometry, study data will be keyed into an Excel database using data forms enabled with validation criteria. An assistant will randomly check 30 % of the keyed data for accuracy. All data will be imported into SAS for final analysis.

Baseline characteristics of all randomized participants will be presented for each group using descriptive statistics. Continuous variables will be reported as numbers of observed and missing values, mean, standard deviation, median and range. Categorical variables will be described as frequencies and percentages.

Analysis of covariance (ANCOVA) regression model will be used to evaluate the main treatment effects on the primary outcome, adjusting for its baseline measure, sex, and important baseline confounding factors. Normality of the continuous outcome data will be tested, and the goodness of model fit will be evaluated. Model-adjusted means will be estimated for each group, and their differences will be tested. A similar approach will be used for other continuous secondary outcomes. Generalized linear models will be applied to categorical outcomes as appropriate. Sensitivity analysis will be conducted on the primary outcome with missing data (if >10 %), using multiple imputations with the MCMC method [82].

Psychosocial variables (i.e. perceived enjoyment, autonomy, competence, relatedness and self-efficacy) related to physical activity will be considered as potential mediators of the intervention (Fig. 5 illustrates the mediation model to be tested; dotted lines indicate hypothesized mediation paths) [83]. The recommendations of Kraemer for testing mediators of intervention effects in randomized clinical trials will be followed [83]. Data permitting, further analyses will evaluate the treatment effects on a subgroup of participants who report having adhered to the intervention.

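### Baseline-adjusted ANCOVA for the accelerometer outcomes, fitted in the ordinary way, drops randomized participants whose 8-week record is valid but whose baseline wear week is not: an avoidable loss of precision

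*Protocol article*

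**What the plan says.** Four statements in the protocol article bear on this.

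- **Wear rule (Secondary outcomes).** The device is worn twice: "Participants are asked to wear the Actigraph following each assessment for seven consecutive days". In processing, "days with less than 600 min of valid records are removed before data analysis", and then "All participants with at least 3 days of valid data will be included in the analysis". The text does not say whether the 3 days are needed at baseline, at 8 weeks or at both.
- **Model (Statistical analyses).** The primary outcome is analysed by ANCOVA, "adjusting for its baseline measure, sex, and important baseline confounding factors". For the rest, "A similar approach will be used for other continuous secondary outcomes". Nothing is said about a participant whose baseline value is missing.
- **Missing data (Statistical analyses).** The general principle is "Treatment evaluation will be performed on the principle of intention to treat". The one missing-data method is multiple imputation, limited as follows: "Sensitivity analysis will be conducted on the primary outcome with missing data (if >10" per cent). Accelerometry is not covered.
- **Timing (Outcome assessments).** "Randomization takes place at a subsequent visit to the participants’ home once baseline accelerometer data collection is completed". No minimum number of valid baseline days is stated as a condition for randomization.

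**The concern.** An ANCOVA that adjusts for baseline needs a baseline value and a follow-up value for each person in the fit. Standard software drops any record with a missing covariate. With the wear rule applied to each week, the model would use only participants who met it twice. Someone who wore the device too little before randomization, was still randomized and then gave a full 8-week record would be left out.

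That loss serves no purpose. The baseline week ends before allocation, so arm cannot have influenced whether it was valid, and the follow-up value carries full information about the treatment comparison. With 17 per arm, each lost participant matters. The Abstract and Discussion present accelerometry as a strength of the trial. The Discussion also lists physical activity among the possible mediators, so the same loss could carry into that analysis.

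**Working it through.** **1. The plan's own figure.** The article gives no calculation for accelerometry, only for the one mile run/walk time: difference 17 s, SD 15 s, 80 % power, two-sided 5 %, adjusted for multiple comparisons. Taking Bonferroni for three pairwise comparisons (alpha = 0.05/3), n per arm = 2 × (2.394 + 0.842)² × (15/17)² = 16.3, rounded up to 17, or 51 in total. Normal-approximation power at 17 per arm is 0.819. The stated size reproduces, and the present point does not touch it.

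**2. Inputs for accelerometry.**
- N = 51 (Sample size).
- m, the chance of an invalid record at a visit: not given. Assumed 10 % or 20 %, independent across visits.
- r, the correlation between baseline and 8-week activity: not given. Assumed 0.4 or 0.6.
- One anchor: Methods/design expects complete data on at least 41 of 51. Independent failure of 10 % per visit gives 51 × 0.9² = 41.3, so the 10 % row matches that target. The target is not specific to accelerometry.

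**3. Numbers analysed.** Valid at both visits: 51(1 − m)². Valid at 8 weeks: 51(1 − m). The difference, 51m(1 − m), is the recoverable group.

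| m | both visits | 8 weeks | recoverable |
|---|---|---|---|
| 10 % | 41.3 | 45.9 | 4.6 |
| 20 % | 32.6 | 40.8 | 8.2 |

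**4. Precision by simulation.** 4000 trials per setting, three arms of 17, standard-normal activity, no true effect. Complete-case ANCOVA was compared with ANCOVA on everyone valid at 8 weeks, with an invalid baseline filled by regression on the baseline activity questionnaire (PAQ-A). Standard errors (SE) of an arm-versus-control difference, in SD units:

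| m | r | complete case | baseline filled | reduction |
|---|---|---|---|---|
| 10 % | 0.4 | 0.362 | 0.345 | 4.7 % |
| 10 % | 0.6 | 0.303 | 0.293 | 3.3 % |
| 20 % | 0.4 | 0.409 | 0.360 | 12.0 % |
| 20 % | 0.6 | 0.353 | 0.324 | 8.2 % |

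Filling with the overall baseline mean, without the questionnaire, gave 0.36 to 0.34 at 10 % and 0.41 to 0.36 at 20 % (r = 0.4). The gain therefore does not depend on the questionnaire. Across these runs the reduction is about 3-6 % at 10 % and about 7-12 % at 20 %.

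**5. Hand check for mean filling.** In large samples the complete-case variance is proportional to (1 − r²)/(1 − m)². With the baseline mean-filled it is proportional to [1 − (1 − m)r²]/(1 − m). The ratio is (1 − r²) / {(1 − m)[1 − (1 − m)r²]}.
- m = 0.1, r = 0.4: 0.84/(0.9 × 0.856) = 1.090, SE 4.2 % smaller.
- m = 0.1, r = 0.6: 0.64/(0.9 × 0.676) = 1.052, SE 2.5 % smaller.
- m = 0.2, r = 0.4: 0.84/(0.8 × 0.872) = 1.204, SE 8.9 % smaller.
- m = 0.2, r = 0.6: 0.64/(0.8 × 0.712) = 1.124, SE 5.7 % smaller.

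These sit a little below the simulated gains, as expected: the formula ignores the extra cost of small and unequal arms.

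**6. Bias.** Both analyses were unbiased when invalid wear did not depend on arm. When follow-up wear was made to depend on arm and activity (m = 20 %, r = 0.4), complete-case bias was −0.27 SD. It was still −0.23 SD after the follow-up was also imputed from the questionnaire.

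**The case against.** The strongest reply is that the article never says these participants are discarded. The wear rule names no visit, the model for secondary outcomes is described only as similar, and the handling of a missing covariate is something an article often leaves to the analysis plan. Randomization after the wear week may also keep invalid baselines rare. This stands to the extent that the need for validity at both visits is inferred from the stated model and not written. But the article does fix the model, the wear threshold and the limit on imputation, and their ordinary execution has the consequence described.

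A reader might also infer that the wear rule contradicts the intention-to-treat principle by setting up a second analysis population. The text does not support that. The rule sits in the data-processing description, after the non-wear and 600-minute rules, and defines when activity counts as measured. A participant below it has a missing outcome. Intention to treat concerns analysis in the arm assigned.

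Two further objections are right and limit the point. Failure of 20 % at each visit implies 0.8 × 0.8 = 64 % complete, or about 33 of 51, well short of the 41 expected; the 10 % row is the one consistent with the article. And the PAQ-A is a seven-day recall completed at the visit, whereas the Actigraph is worn in the seven days afterwards. The cited correlation of 0.49 may not apply across different weeks, so the argument should not rest on it.

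**Conclusion.** The point holds as an avoidable loss of precision on one secondary outcome. With 10 % invalid wear per visit, four or five randomized participants with valid 8-week data would be lost, and recovering them makes the standard error about 3-6 % smaller. With 20 %, about eight would be lost and the reduction is about 7-12 %. These sizes rest on assumed failure rates, independence between visits, a baseline to follow-up correlation of 0.4 to 0.6, and a complete-case fit.

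The primary analysis and the sample size are unaffected. It would be tempting to add that the planned analysis is biased. The documents do not show that: no pattern of wear by arm is given, and where wear was made to depend on arm and activity, the change examined removed little of the bias.

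**What to change.** - **Secondary outcomes.** State that at least 3 valid days defines a valid accelerometer record at each visit.
- **Statistical analyses.** State that the accelerometer outcomes are analysed for every randomized participant with a valid 8-week record. Handle an invalid baseline in one of two ways: (a) a mixed model with baseline and 8-week activity both as responses and arm means constrained equal at baseline; or (b) the planned ANCOVA with the missing baseline filled from pre-randomization data only. For (b) the overall baseline mean is enough, and PAQ-A is optional. The precision figures above were obtained for (b).
- **Reporting.** Give the number of participants without a valid record, by arm and visit.

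The cost is a few sentences and a few lines of SAS code, with slightly more analysis work. No new data, visits or participants are needed. The change does not recover participants whose 8-week record is invalid, and it does not remove bias if follow-up wear depends on unobserved activity.

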
### Statistical analyses

Treatment evaluation will be performed on the principle of intention to treat. Statistical analyses will be conducted using SAS version 9.3 software (SAS Institute, Cary, NC, USA). All statistical tests will be two-sided and maintained at a 5 % significance level. Apart from accelerometry, study data will be keyed into an Excel database using data forms enabled with validation criteria. An assistant will randomly check 30 % of the keyed data for accuracy. All data will be imported into SAS for final analysis.

Baseline characteristics of all randomized participants will be presented for each group using descriptive statistics. Continuous variables will be reported as numbers of observed and missing values, mean, standard deviation, median and range. Categorical variables will be described as frequencies and percentages.

Analysis of covariance (ANCOVA) regression model will be used to evaluate the main treatment effects on the primary outcome, adjusting for its baseline measure, sex, and important baseline confounding factors. Normality of the continuous outcome data will be tested, and the goodness of model fit will be evaluated. Model-adjusted means will be estimated for each group, and their differences will be tested. A similar approach will be used for other continuous secondary outcomes. Generalized linear models will be applied to categorical outcomes as appropriate. Sensitivity analysis will be conducted on the primary outcome with missing data (if >10 %), using multiple imputations with the MCMC method [82].

Psychosocial variables (i.e. perceived enjoyment, autonomy, competence, relatedness and self-efficacy) related to physical activity will be considered as potential mediators of the intervention (Fig. 5 illustrates the mediation model to be tested; dotted lines indicate hypothesized mediation paths) [83]. The recommendations of Kraemer for testing mediators of intervention effects in randomized clinical trials will be followed [83]. Data permitting, further analyses will evaluate the treatment effects on a subgroup of participants who report having adhered to the intervention.

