## Methods/design

An eight-week, three-arm parallel randomized controlled trial will be conducted in Auckland, New Zealand with a total of 51 eligible participants. The primary outcome is cardiorespiratory fitness at 8 weeks after randomization. We hypothesize that participants who receive a smartphone app will have greater cardiorespiratory fitness compared to the control group. Secondarily, we hypothesize fitness, physical activity levels, self-efficacy, enjoyment and psychological needs satisfaction will be greater in the immersive app group compared to the non-immersive app group at 8 weeks after randomization. We also expect that recruitment goals will be met, attrition will be low, and that we will be able to collect complete data on at least 80 % (41/51) of participants.

The protocol is in accord with the SPIRIT 2013 statement [52, 53], and the intervention is described according to the CONSORT-EHEALTH checklist [54]. See Additional file 1 for the complete checklist.

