### Sample size

A total sample of 51 participants (17 per group) will provide 80 % power at 5 % level of significance (two-sided) to detect a minimal difference of 17 s in time to complete the one mile run/walk test at 8-week post randomization between the treatment groups. This has assumed a standard deviation of 15 s on the primary outcome, with adjustment for multiple comparisons. Based on normative data [57] for this population, the calculation assumes a mean baseline value of 10-min to complete the one mile/1.6 Km run/walk test. An improvement in the completion time of 78 s for this distance corresponds to a shift from the 25^th^ to the 50^th^ percentile in terms of cardiorespiratory fitness, which is considered a meaningful impact towards a more favorable cardiovascular profile.

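### The sample size pays for a multiplicity adjustment that the analysis section does not apply; as written, the familywise error for the two primary app-versus-control contrasts is about 9 %

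*Protocol article*

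**What the plan says.** The Sample size section states that "A total sample of 51 participants (17 per group) will provide 80 % power" at a two-sided 5 % level, "to detect a minimal difference of 17 s in time to complete the one mile run/walk test". On the assumptions behind this it adds: "This has assumed a standard deviation of 15 s on the primary outcome, with adjustment for multiple comparisons". It names neither the method of adjustment nor the number of comparisons.

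The Statistical analyses section sets the general rule: "All statistical tests will be two-sided and maintained at a 5 % significance level". For the primary outcome it specifies an ANCOVA and continues: "Model-adjusted means will be estimated for each group, and their differences will be tested". It does not mention an adjustment, an order of testing, or a condition that an overall test be significant first.

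The primary aim, at the end of the Background, is to compare the two apps with usual behavior. Methods/design words the primary hypothesis as "We hypothesize that participants who receive a smartphone app will have greater cardiorespiratory fitness compared to the control group". The comparison of the immersive with the non-immersive app, which also covers fitness, is introduced there as secondary.

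**The concern.** Three arms give three pairwise differences on the primary outcome. The sample size was enlarged so that several comparisons could be made under control, but the analysis rule, read literally, gives each comparison its own 5 %. An analyst who follows the analysis section drops the protection for which the extra participants were recruited. An analyst who follows the sample size section departs from the literal analysis rule.

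At stake is the error rate of the trial's main effectiveness claim. The primary hypothesis refers to receiving an app without saying whether one app, either app or both must beat control. If either app's contrast can carry the claim, there are two chances of a false positive at 5 % each.

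**Working it through.** **Inputs.** From Sample size: 17 per group, 80 % power, two-sided 5 %, difference 17 s, SD 15 s. From Randomization and blinding: three arms, 1:1:1. Residual degrees of freedom without covariates: 3 × 17 − 3 = 48.

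**Step 1: reproduce the stated size.** Normal formula per group: n = 2 (SD/difference)² (z₁₋α/₂ + z₀.₈₀)², with 2 × (15/17)² = 1.557 and z₀.₈₀ = 0.842.

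| Level per test | z₁₋α/₂ | n before rounding | n per group |
|---|---|---|---|
| 0.05 (unadjusted) | 1.960 | 12.2 | 13 |
| 0.05/2 | 2.241 | 14.8 | 15 |
| 0.05/3 | 2.394 | 16.3 | 17 |

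The stated 17 matches 0.05/3, a Bonferroni split over three pairs. Against the unadjusted figure, the adjustment adds 3 × (17 − 13) = 12 participants. The match does not prove which method was used. A t-based calculation at 0.05/2 gives 16 or 17 (three-group or two-group degrees of freedom), and Tukey at 17 per group gives 80.8 % power. An unadjusted t-based calculation gives only 13 or 14.

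**Step 2: error rate of the analysis as written.** All arms are equal, 17 per group, pooled variance on 48 df, each test two-sided at 5 % (critical t = 2.011).

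| Event | Probability |
|---|---|
| At least one of the two app-versus-control contrasts significant | 9.0 % |
| At least one app significantly faster than control | 4.5 % |
| One given app significantly faster than control | 2.5 % |
| At least one of all three pairs significant | 12.1 % |

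The first two rows come from simulations of 1,000,000 trials. The last is the exact studentized-range probability, which simulation confirms (12.0 to 12.1 %). The contrasts share arms, so these figures lie below the values for independent tests: 1 − 0.95² = 9.75 % and 1 − 0.95³ = 14.3 %.

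**Step 3: what control would cost.** Power for one app-versus-control contrast at 17 s / 15 s and 17 per group (t-based, 48 df), and familywise error over the three pairs when all arms are equal:

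| Procedure | Power | Familywise error |
|---|---|---|
| Unadjusted 5 % | 90 % | 12.1 % |
| Bonferroni, three pairs | 79 % | 4.3 % |
| Tukey, three pairs | 81 % | 5.0 % (by construction) |
| 2-df arm test at 5 %, then pairwise tests at 5 % | 82 to 88 % | 5.0 % |

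For the last row, power is 88 % if both apps have the 17 s effect or only one does, and 82 % if the other app has half of it. With three arms this is a closed test: if any two of the pairwise equalities hold, all three arms are equal, and the overall test covers that case.

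**The case against.** The strongest reply is that the two sections need not conflict. The Sample size section itself puts "5 % level of significance (two-sided" and an adjustment in the same calculation, so 5 % may mean the overall level throughout. The article never says that the tests are unadjusted, and the name of a procedure is commonly left to an analysis plan. The ANCOVA paragraph also mentions evaluating the main treatment effects before the pairwise differences, which would fit an overall test first.

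Part of this stands. An overall 5 % is a possible intention, and not naming the method would be no fault in itself. But the sentence applies 5 % to every statistical test, and nothing makes the pairwise tests conditional on an overall one. The point rests on two stated rules that give different error rates, not on missing detail.

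A reader might also infer three stronger things that the article does not support:

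- **That the false-claim rate for the primary hypothesis is 12 %, more than twice nominal.** That figure counts immersive versus non-immersive, which the protocol makes secondary. A significant difference between the apps would not meet the primary hypothesis. The rate for the two primary contrasts is about 9 %, or 1.8 times nominal, and includes results in which an app looks worse than control.
- **That Tukey was the method assumed.** No method is named, and several fit 17 per group.
- **That the trial is underpowered for this reason.** The sample size already covers the adjustment, to within about a percentage point of 80 % under Bonferroni.

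**Conclusion.** Wrong as written, of moderate severity. The analysis rule, taken literally, does not carry out the adjustment on which the sample size rests. The resulting familywise error is about 9 % for the two primary contrasts (about 4.5 % for falsely finding an app faster, against 2.5 % for one contrast). It is about 12 % only if the secondary app-versus-app contrast on fitness is included.

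These figures assume that all three arms are truly equal, that there are 17 analyzed per group with normal errors and a common variance, that a significant result for either app can support the claim, and that there is no gate before the pairwise tests. If the overall arm test was meant as a gate, or if 5 % was meant as the familywise level, the error is controlled and only the wording needs correction.

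**What to change.** Reconcile Statistical analyses with Sample size. State that the two-sided 5 % level on the primary outcome is familywise across the between-group comparisons, and name one procedure that matches the adjustment used in the sample size calculation. If that record shows Bonferroni or Tukey over the three pairs, say so. A 2-df arm test at 5 %, followed by pairwise tests at 5 % only if it is significant, would also control the error. Keep the two app-versus-control differences as primary and immersive versus non-immersive as secondary, and say whether either app beating control is enough to support the primary hypothesis.

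Trial status reports that follow-up is complete and analysis is under way. The procedure should therefore be fixed and dated before the group comparisons are looked at. If they have already been seen, report that and take the procedure from the original sample size record.

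The cost is one sentence, with the same sample size, model and software. Under Bonferroni or Tukey, power for a single contrast falls from about 90 % to about the 80 % that the protocol states. Some contrasts with p just below 0.05 would no longer count as significant.
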